#### Exploring the patient experiences and perspectives of IMT load

Participant experience of IMT will be explored after each load. As participants will have a range of communication abilities, the researchers will work with speech and language therapists and staff in the ICU to optimise participants’ ability to communicate and express their experience of IMT. Communication methods will include the following: inline speaking valve, above cuff vocalisation, electrolarynx, bespoke communication boards, facial expressions, written communication and mouthing.^39^,^41^ An indicative topic guide to guide enquiry was co-developed and tested with the project’s PPI group.

Perceived breathing difficulty and unpleasantness will be measured using 0–10 numeric rating scales, as previously described^31^ with anchor points informed by the study PPI group: “0=none”, “10=extreme” for breathing unpleasantness (online supplemental file 1), “0=easy”, “10=extremely difficult” for breathing difficulty (online supplemental figure 2).

In participants who can phonate or respond using mouthing or written communication, following completion of the difficulty numeric rating scale (online supplemental figure 2), the participant will be asked “can you explain in words what that number felt like?” Due to the complexity of needs in this population, the researcher will use a range of strategies to enhance the depth of enquiry, such as confirmatory paraphrasing and summarising back to participants to check understanding of their response.

In participants unable to engage in independent expression of feelings as detailed above and to supplement information gained by verbal, written or lip reading, bespoke communication boards will be used (online supplemental figures 3–6). Within this complex population, when factors such as difficulty in phonating, breathlessness, weakness or fatigue with written communication limit answers, the bespoke communication boards will help improve the depth of information obtained. Contextual information (eg, participant gestures and the environment) will be captured using field notes, audio and/or video recording (subject to optional participant consent for video).

Participants will perform all study procedures on up to three occasions over a 7-day period. Reasons for earlier withdrawal would include decannulation from tracheostomy, weaning from mechanical ventilation, withdrawal of consent, or death. Table 1 provides an overview of study interventions and assessments performed during the study period.

**Table 1 T1:** Overview of study procedures

Study procedures	Study period	
	Day 0 (enrolment)	Each study occasion
Baseline characteristics	●	
SOFA score		●
Ventilation and cardiovascular parameters		●
Maximal inspiratory pressure (PImax)		●
Inspiratory muscle activity		●
Airway pressure and flow		●
Inspiratory muscle training		●
Perceived difficulty and unpleasantness (NRS)		●
Qualitative data enquiry		●

NRS, numerical rating scale; SOFA, sequential organ failure assessment.

### Data analysis plan

#### Quantitative

Data will be assessed for normality using histograms and the Shapiro-Wilk test. Baseline characteristics will be presented as mean (SD) or median (IQR). Mean peak root-mean-squared values of EMGdia, parasternal intercostal, scalene and sternocleidomastoid EMG for each load will be normalised as a ratio to that obtained during unsupported spontaneous breathing. For each individual muscle, the EMG activity between different IMT loads will be compared using a one-way ANOVA or Kruskal-Wallis test. To evaluate patterns of muscle activity between sEMG of the parasternal intercostal, scalene and sternocleidomastoid muscles and EMGdia, plots will be visually evaluated on Prism (GraphPad Software Inc, California, US) to identify the IMT load inducing maximum diaphragmatic contribution before the upward inflection point of accessory muscle activity.

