### Study procedures

#### Measurement of inspiratory muscle activity

Electrical activity of the diaphragm (EMGdia) will be measured using an oesophageal multipair catheter (NAVA, Getinge, Sweden), inserted according to manufacturer guidelines. The catheter will be inserted into the participant’s nose and passed into the stomach using the distance from the nasal bridge to the earlobe to xiphoid process measurement. The catheter will be connected to a ventilator (Servo-I, Getinge, Sweden), loaded with software (Servotracker, Getinge, Sweden), to verify catheter placement and to perform amplification and digital processing of EMGdia signals using the system’s proprietary algorithms. The Servo-I will only be used for acquisition of EMGdia data, not for mechanical ventilation.

Parasternal intercostal, scalene and sternocleidomastoid muscle activity will be measured using surface electromyography (sEMG). Skin will be prepared by shaving the area (if necessary) and lightly abrading the skin with Nuprep skin preparation gel (Weaver and Company, Aurora, USA) before wiping with an alcohol-impregnated wipe to remove sebum and dead skin cells before application of silver-silver-chloride electrodes. Parasternal intercostal EMG will be obtained with electrodes positioned over the second intercostal space bilaterally.^35^ Scalene and sternocleidomastoid electrodes will be positioned over the inferior portion of each muscle as previously described.^36^ EMG signals will be amplified (gain 1000) and band-pass filtered (20–1000 Hz with additional 50 Hz adaptive mains filter, (BioAmp amplifier, ADInstruments, Sydney, Australia)) and digitised (sampling frequency 2 kHz, PowerLab 16/35, ADInstruments, Sydney, Australia) before being displayed on a laptop computer for analysis.

Root-mean-squared values of EMG signals will be calculated in LabChart 7 (ADInstruments, Sydney, Australia) and Servotracker (Getinge, Sweden) and mean peak RMS EMG value per breath at each IMT load will be expressed as a ratio to that obtained while breathing during unsupported spontaneous breathing.

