#### Breathing conditions measured

Respiratory muscle activity, airway pressure and airway flow will be measured during the following breathing conditions: (1) spontaneous breathing supported by mechanical ventilation with pressure support, with settings maintained unchanged from those determined by the attending intensivist; (2) unsupported spontaneous breathing through tracheostomy after disconnection from mechanical ventilation; (3) during four IMT loads.

During spontaneous breathing supported by mechanical ventilation, the participant will receive no additional instructions from the researcher; measurements will be taken for 5 min. During unsupported spontaneous breathing and IMT, the participant will be informed that their breathing will feel harder. The researcher will count each of the ten breaths at each IMT load to guide the participant. Participants will be coached to exhale fully prior to each IMT breath and be given strong verbal encouragement to inhale forcefully against the applied resistance to generate tidal volume up to a comfortable deep inspiration at their own pace; no set breathing frequency will be imposed.

IMT will be performed using a tapered-flow resistive loading device (POWERbreathe KH2, POWERbreathe, Southam, UK). Participants will perform IMT at 15, 30, 45 and 60% of their maximal inspiratory pressure (PImax) in a randomised order (Sealed Envelope, Oxford, UK). The IMT loads chosen are based on preliminary data from healthy participants (study approved by Brunel University of London: reference 45378-MHR-Jan/2024-49666-3; manuscript in preparation)**,** where we found an increase in diaphragm activity with increasing IMT load, which, from 30–40% of PImax was accompanied by a proportionally greater increase in extra-diaphragmatic muscle activity. We have therefore chosen loads spanning the inflection point seen in healthy participants, with the aim of identifying a load which maximises diaphragm activity but which minimises accessory muscle activity.

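### EMG ratios: an implied normality check picks ANOVA or Kruskal-Wallis muscle by muscle, and neither test uses the fact that each participant performs all four loads

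*Protocol article*

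**What the plan says.** The Quantitative part of the Data analysis plan opens with "Data will be assessed for normality using histograms and the Shapiro-Wilk test". EMG values "for each load will be normalised as a ratio to that obtained during unsupported spontaneous breathing", and no transformation is mentioned. Then: "For each individual muscle, the EMG activity between different IMT loads will be compared using a one-way ANOVA or Kruskal-Wallis test".

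Under Breathing conditions measured, the loads are varied within each participant: "Participants will perform IMT at 15, 30, 45 and 60% of their maximal inspiratory pressure (PImax) in a randomised order". Study procedures are repeated on up to three occasions within 7 days.

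The load is then chosen by looking at plots of the accessory muscles and the diaphragm, "to identify the IMT load inducing maximum diaphragmatic contribution before the upward inflection point of accessory muscle activity". The article does not say whether the plots show means, medians or individual curves.

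**The concern.** The outcome is a positive ratio, for which right skew and multiplicative differences between patients are to be expected. The plan has no log scale. It offers two tests and, by implication, lets the look of the data choose between them for each muscle. Three things follow.

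- The diaphragm could be summarised by means and an accessory muscle by ranks, although the aim is to compare their patterns.
- A muscle sent to Kruskal-Wallis has a p-value but no estimate of how much activity rises between loads.
- One-way ANOVA and Kruskal-Wallis, as named, compare independent groups. Stable differences between patients, which a crossover of loads is designed to remove, stay in the error term.

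At stake is the ability to show how each muscle responds to load, with an estimate and an interval, in a study meant to inform a feasibility trial.

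**Working it through.** **Inputs from the protocol.** 40 participants; four muscles; four loads, all within participant; the outcome is a ratio to unsupported breathing. No SD, effect size, significance level or power is given, so there is no stated figure to reproduce.

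**Assumptions (not in the protocol).** Log-normal ratios, log-SD 0.1 to 1.0, within-participant correlation 0.6, independent muscles, one occasion each, all tests at 0.05.

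**Step 1: how often muscles get different tests.** If a muscle fails Shapiro-Wilk with probability a, four equally skewed muscles split with probability 1 − a⁴ − (1 − a)⁴. At log-SD 0.3 with one load tested: 1 − 0.469⁴ − 0.531⁴ = 1 − 0.048 − 0.080 = 0.872.

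| log-SD | a, one load tested | split | a, any of four loads fails | split |
|---|---|---|---|---|
| 0.1 | 0.109 | 0.370 | 0.337 | 0.794 |
| 0.2 | 0.236 | 0.656 | 0.615 | 0.835 |
| 0.3 | 0.469 | 0.872 | 0.870 | 0.427 |
| 0.5 | 0.850 | 0.477 | 0.997 | 0.012 |
| 0.8 | 0.994 | 0.024 | 1.000 | 0.000 |

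With unequal log-SDs of 0.2, 0.3, 0.5 and 0.7 across the muscles, the split is 0.91 (one load) or 0.45 (any load). With exactly normal data and one test per muscle it is 1 − 0.95⁴ − 0.05⁴ = 0.19. A split is likely at mild to moderate or unequal skew, and rare when all muscles are strongly skewed.

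**Step 2: cost of ignoring the pairing.** Take two loads, a true log rise of 0.16 (exp(0.16) = 1.17, a 17% rise) and within-participant log-SD 0.25 per observation.

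- Paired: the standard error is 0.25 × √(2/40) = 0.056. The effect is 0.16/0.056 = 2.86 standard errors, which gives power of about 80%.
- Unpaired, between-participant log-SD 0.4: the assumed standard error is √(0.25² + 0.4²) × √(2/40) = 0.472 × 0.224 = 0.1055. Significance needs a difference of 1.96 × 0.1055 = 0.207. The actual sampling error is still 0.056, so power is P(Z > (0.207 − 0.16)/0.056) = P(Z > 0.84) = 20%.
- Simulated Kruskal-Wallis power is 21%, 3% and 0.2% at between-participant log-SD 0.4, 0.6 and 0.8.

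Simulated power with all four loads (correlation 0.6; log means rising by 0, 0.2, 0.4 and 0.6 of the log-SD):

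| log-SD | Route chosen by Shapiro-Wilk, unpaired | Log one-way ANOVA, unpaired | Log scale, participant in model |
|---|---|---|---|
| 0.3 | 0.561 | 0.594 | 0.973 |
| 0.5 | 0.535 | 0.567 | 0.973 |
| 0.7 | 0.560 | 0.593 | 0.976 |
| 1.0 | 0.574 | 0.614 | 0.983 |

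The pre-test route loses 3 to 4 points against an unpaired log analysis. Keeping participant in the model gains a further 37 to 41 points. With no load effect, the unpaired tests rejected in at most 0.4% of runs, and the paired log analysis in 4.2% to 5.0%.

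**Step 3: the conditional upturn.** For log-normal ratios, arithmetic mean = geometric mean × exp(s²/2). Take geometric means 1.3, 1.6, 1.9 and 2.2 (equal steps).

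- Log-SD 0.3, 0.4, 0.5, 0.6: arithmetic means 1.360, 1.733, 2.153, 2.634; steps 0.374, 0.420, 0.481. The last step is 29% larger than the first.
- Log-SD rising evenly from 0.3 to 0.7: arithmetic means 1.360, 1.757, 2.231, 2.811; steps 0.398, 0.473, 0.580. The last step is 46% larger.

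With geometric means 1.5, 2.0, 2.5 and 3.0, a constant log-SD of 0.5 gives steps of 0.57 throughout, and a log-SD falling from 0.6 to 0.3 gives 0.47, 0.44 and 0.43. In neither case is there an upturn.

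**The case against.** **The selector is not stated.** The check uses histograms as well as Shapiro-Wilk, has no threshold or unit, and is followed directly by a sentence on baseline characteristics. This stands: the split rates in Step 1 illustrate one possible rule. But the plan offers no other criterion for its choice of test.

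**One-way ANOVA could be shorthand for the repeated-measures version.** Possibly, but its named alternative is Kruskal-Wallis, an independent-groups test. The rank counterpart for repeated measures would be Friedman.

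**A reader might infer that mixed tests distort the choice of load.** The document does not support that. The tests run within each muscle, while muscles are compared by eye on plots, and all are normalised the same way. Mixed tests affect the reported tests and effect estimates only.

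**A reader might infer that the pre-test costs the precision lost by averaging raw ratios.** That loss is real under marked skew, but Shapiro-Wilk would then nearly always reject: in 94% to 99.9% of runs at between-participant log-SD 0.4 to 0.8. The plan would seldom use raw means there, and Kruskal-Wallis gives the same p-value with or without logs.

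**A reader might infer that a false upturn is built in.** It needs relative spread that grows with load and plots of arithmetic means over participants. The document states neither. The mean in "mean peak RMS EMG value per breath at each IMT load will be expressed as a ratio" is over breaths within a participant. Geometric means also do not remove the risk. With straight-line medians and log-SD rising from 0.3 to 0.75, the last step exceeded 1.5 times the first in 22% of simulated studies, against 50% for arithmetic means.

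**The study is exploratory,** with no formal sample size calculation. That lowers the stakes, but a better method costs almost nothing.

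**Conclusion.** The point holds in a limited form. The plan names two unpaired tests on untransformed ratios and implies a data-driven choice between them for each muscle. Different muscles may be tested differently, with no effect size on the rank branch. The main loss is from ignoring the within-participant design: about 40 points of power under a correlation of 0.6, more if patients differ more from each other and less if they differ less. The pre-test adds only 3 to 4 points. All these sizes rest on assumed log-normal data, because the protocol gives no variability. The upturn is a conditional risk, and no bias in the choice of load has been shown. This is a cheap improvement.

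**What to change.** - Drop the normality check as the method selector for EMG.
- Analyse ln(EMG ratio) for all four muscles with the same within-participant model: load as a factor, random effects for participant and occasion. Check the residuals of that model.
- Report geometric mean ratios with 95% confidence intervals.
- Plot geometric means, back-transformed to the ratio axis, alongside individual curves. State that the upward inflection is judged on that axis, since a straight line in ratios is concave in logs.
- Keep a rank-based within-participant test, such as Friedman, as a sensitivity analysis.

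The cost is a few sentences of analysis text and no change to data collection. The downside is that results read as geometric mean ratios, which need a line of explanation.

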**Methods:**

This study is designed as a prospective, mixed methods study. Forty difficult to wean, tracheostomised patients on mechanical ventilation will perform IMT at 15, 30, 45 and 60% of their maximal inspiratory pressure (PImax) in a randomised order using a tapered flow resistive loading device (POWERBreathe KH2, POWERBreathe, UK). Electrical activity of the diaphragm will be measured using an oesophageal multipair catheter (NAVA, Getinge, Sweden); extra-diaphragmatic (parasternal, scalene and sternocleidomastoid) muscle activity will be measured using surface electromyography. Patient experience of each load will be explored by measuring perceived breathing difficulty and unpleasantness using 0–10 numeric rating scales, verbal or written communication techniques in line with the participants' communication ability, and/or bespoke communication boards co-designed with the study patient and public involvement (PPI) group. Quantitative and qualitative data will be integrated to inform a diaphragm-focused, patient-acceptable IMT load.

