### Sample size calculation

This is the first study of its kind to measure inspiratory muscle activity and explore patient experience during different IMT loads in mechanically ventilated patients. No formal sample size calculation has been performed; however, based on data from the healthy study data conducted by our group, and accounting for the anticipated heterogeneity in the ICU population, we hypothesise that studying 40 participants will allow adequate exploration across one to three study occasions.

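### The four loads are compared with tests for independent groups, although every participant performs all four, so p-values are miscalibrated and power is usually lost

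*Protocol article*

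**What the plan says.** The design is within-participant. Under Breathing conditions measured: "Participants will perform IMT at 15, 30, 45 and 60% of their maximal inspiratory pressure (PImax) in a randomised order". The abstract gives 40 participants. The paragraph above Table 1 adds: "Participants will perform all study procedures on up to three occasions over a 7-day period". Each person can therefore supply up to 4 × 3 = 12 load values per muscle.

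The Quantitative part of the data analysis plan says that mean peak EMG "for each load will be normalised as a ratio to that obtained during unsupported spontaneous breathing", and then: "For each individual muscle, the EMG activity between different IMT loads will be compared using a one-way ANOVA or Kruskal-Wallis test". To choose the load, "plots will be visually evaluated on Prism". Under Sample size calculation: "No formal sample size calculation has been performed".

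The article mentions no repeated-measures ANOVA, Friedman test, mixed model or participant effect, and no rule for combining a participant's occasions.

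**The concern.** One-way ANOVA and Kruskal-Wallis treat the values at 15, 30, 45 and 60% of PImax as four separate groups of people. Here they are four measurements on the same people. Having each participant act as their own control removes stable differences between participants from the load comparison. The named tests put those differences back into the error term. The sample size section expects such differences, since it speaks of "accounting for the anticipated heterogeneity in the ICU population".

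This is the only between-load test named in the plan, and it serves objective 1. A real load effect on the diaphragm or an accessory muscle could be reported as non-significant. The normality check does not help, because it selects between two tests that both ignore the pairing.

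**Working it through.** The article gives no alpha, effect size, SD or correlation, so there is no stated figure to reproduce. From the documents: 40 participants, 4 loads, 1 to 3 occasions, and the named tests. Everything else below is an assumption, shown as a range, with a nominal level of 5%.

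**1. Which test is meant.** One-way ANOVA alone might loosely mean a one-way repeated-measures ANOVA. The rank alternative named beside it is Kruskal-Wallis, which is for independent groups. The paired counterpart would be Friedman. The text therefore supports the independent-groups reading.

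**2. Variance of a load contrast, one value per participant per load.** Let each value have variance σ² and let two loads in one participant correlate at r.

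- True variance of a difference between two load means: 2σ²(1-r)/n.
- Variance assumed by the independent-groups test: 2σ²/n.
- Overstatement: 1/(1-r). At r = 0.5 this is 1/0.5 = 2. At r = 0.7 it is 1/0.3 = 3.3.
- True SE divided by assumed SE: √(1-r), which is 0.84, 0.71, 0.55 and 0.32 at r = 0.3, 0.5, 0.7 and 0.9.

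**3. Simulation, one occasion** (4,000 trials per row, total variance 1, linear trend; power is for an assumed rise of 0.5 SD from lowest to highest load).

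| r | Type I error, one-way ANOVA | Type I error, Kruskal-Wallis | Power, one-way ANOVA | Power, repeated-measures ANOVA |
|---|---|---|---|---|
| 0.3 | 0.010 | 0.013 | 41% | 63% |
| 0.5 | 0.003 | 0.002 | 34% | 79% |
| 0.7 | <0.001 | <0.001 | 29% | 96% |
| 0.9 | <0.001 | <0.001 | 17% | 100% |

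The type I error of repeated-measures ANOVA and Friedman stays between 0.04 and 0.05 throughout.

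**4. Simulation, 1 to 3 occasions pooled as rows** (1,500 trials per scenario). Assumed log-scale SDs are participant 0.5, occasion 0.2, participant-by-load 0.10 and residual 0.15. The implied correlation between loads on one occasion is (0.25 + 0.04)/(0.25 + 0.04 + 0.01 + 0.0225) = 0.29/0.3225 = 0.90. The repeated-measures test is Hotelling's T² on contrasts of participant means.

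| Rise per load step | Rise from 15 to 60% of PImax | One-way ANOVA rejects | Repeated-measures test rejects |
|---|---|---|---|
| 0% | none | 0.0% | about 5% |
| 5% | 1.05³ = 1.16 | about 2% | about 96% |
| 10% | 1.10³ = 1.33 | about 90% | 100% |

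At the 5% step, ANOVA power depends heavily on the participant SD: about 65% at 0.2, about 34% at 0.3 and 0% at 0.7.

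**5. The opposite direction.** If three occasions each are pooled as independent rows and response to load varies between participants, ANOVA can reject too often under the null:

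- Step 4 SDs with participant-by-load raised to 0.4: about 7%. With 1 to 3 occasions instead of three each: about 3%.
- Participant 0.2, occasion 0.1, participant-by-load 0.4, residual 0.1: about 32%. Participant-by-load is then 0.16/0.22 = 73% of the total variance. If occasions are averaged first: about 2%.
- Total variance 1, with a participant-by-load share of 0.3, 0.5 or 0.6: 0.09, 0.23 and 0.32. Repeated-measures ANOVA on participant means stays at about 0.05.

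**The case against.** **The ratio to unsupported breathing removes differences between participants.** In part it may, and that would lower r. It does not make the values independent: the four ratios on an occasion share one denominator and one participant.

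**The details belong in the full protocol or SAP.** This stands for how occasions are combined, on which the article is silent. A reader might infer that repeat occasions enter as new participants, so that some people count three times and false positives are inflated. The text does not say so, and the inflated rates in step 5 apply only under that reading together with marked participant-by-load variation. It does not stand for the test itself, which the article names.

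**The power figures are selective.** This stands in part. The step 4 scenario implies r of about 0.90, and a 5% step is a modest effect over a fourfold rise in load. At 10% per step ANOVA already finds the effect in about 90% of trials. The direction of the loss holds at every positive r with one value per load; its size is unknown.

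**The load is not chosen by this test.** This stands. The plan picks it from plots and then integrates it with the qualitative data, so a wrong p-value does not in itself give a wrong load. A reader might also expect the error bars on those plots to be wrong. The plan mentions none, so that would follow only if intervals were taken from the independent-groups analysis.

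**Conclusion.** The point holds: the named tests are wrong for a design in which each participant performs all four loads. With one value per participant per load and positive correlation, p-values are too large and power is lost, with contrast variance overstated 2-fold at r = 0.5 and 3.3-fold at r = 0.7. The practical loss runs from severe to slight, depending on the assumed effect and variance components. Inflated false positives are a conditional risk only, about 7% to 32% in assumed scenarios with three pooled occasions each. The damage is to the objective 1 load comparison and does not directly determine the chosen load. All sizes rest on assumed SDs and correlations, because the article gives none.

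**What to change.** Replace the comparison sentence with a within-participant analysis, for example:

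> For each muscle, the log EMG ratio will be analysed in a linear mixed model with load, period and occasion as fixed effects and participant and occasion within participant as random effects, adding participant-by-load if it can be estimated. Ratios between loads will be reported with 95% confidence intervals.

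The condition on participant-by-load matters because it cannot be separated from residual variation in anyone with a single occasion.

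The minimum alternative is repeated-measures ANOVA or the Friedman test on one value per participant per load, taken as the mean over that participant's occasions. This also settles how occasions are combined.

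Drop the Shapiro-Wilk choice between one-way ANOVA and Kruskal-Wallis for this comparison only. Keep the normality check for the baseline summaries, where it guides mean (SD) or median (IQR).

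The cost is wording in the protocol or SAP and, for the preferred option, mixed-model software. No new data are needed.
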